### Sample selection

2.3

Patients undergoing their first‐ever specialized assessment for unprovoked seizures or epilepsy with onset after age 50, who also receive a vascular risk factor evaluation (minimum requirements are outlined in Table 1) in conjunction with their initial consultation (within 1 month), are invited to participate in a prospective one‐year trial. Individuals unable to provide informed consent and those with established progressive brain disease, that is, brain tumor or neurocognitive disorder, will be excluded. Notably, we will not exclude patients already on primary or secondary cardiovascular prevention; thus, the study will include groups for whom the benefit from the intervention may be limited.

In addition, we will conduct a system‐level register‐based cohort study based on data from the National Patient Register (NPR), which covers information on all specialized health care encounters in Sweden, and the Swedish Prescribed Drug Register (SPDR), which encompasses details of all prescribed drugs dispensed at pharmacies. Patients aged ≥50 with a first‐ever outpatient appointment to one of the participating clinics and a first‐listed diagnostic code for seizures or epilepsy (ICD‐10: R568, G40) are included. Exclusion criteria will be (i) preexisting seizures/epilepsy, as demonstrated by a registered diagnostic code for seizures (ICD‐10: R568, G40, G41) or a dispensed antiseizure medication (ATC‐code: N03) more than 3 months before the initial consultation, (ii) a registered diagnostic code for stroke or TIA (ICD‐10: I61, I63, I64, or G45 except G454) before the initial consultation, or (iii) progressive brain disease, as indicated by diagnostic codes or drug prescriptions suggestive of brain tumors (ICD‐10: C71, D33, D43, C793) or neurocognitive disorders (ICD‐10: F00‐F03, F051, G30, G318, G912; ATC code: N06D). The only difference in eligibility criteria between the intervention group and the control group will be the period of recruitment; the former will consist of patients with their initial consultation in the 2 years following the “briefing and implementation phase” of the center, whereas the control group will encompass those seen in the four preceding years at the same site.

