### Outcomes

2.4

The purpose of the prospective single group trial is to assess the prevalence of vascular risk factors and the impact of screening on subsequent management and vascular risk. The primary outcome is the proportion of cases receiving pharmacological intervention following the vascular risk factor evaluation; pharmacological intervention is defined as the initiation or dose adjustment of antihypertensive agents, antidiabetic agents (including SGLT2 inhibitors used for other indications), lipid‐lowering agents, antiplatelet agents, or anticoagulants (Table 2). Secondary outcomes are as follows: (i) proportion of cases where the screening procedure uncovers previously undetected vascular risk factors, subdivided into hypertension, diabetes mellitus, moderate‐to‐severe chronic kidney disease, and atrial fibrillation, (ii) alterations in modifiable vascular risk factors at the one‐year follow‐up compared to baseline measurements, (iii) changes in SCORE2/SCORE2‐OP risk scores at the one‐year follow‐up, specifically in individuals without established cardiovascular disease, (iv) proportion of participants with adverse effects following pharmacological intervention, (v) proportion with arrythmias or QT‐prolongation captured during admissions, and (vi) proportion of participants remaining on initiated treatment at the 12‐month follow‐up.

**TABLE 2 epi412987-tbl-0002:** Variables and outcomes for the two analyses.

Variables	Primary outcome	Secondary outcomes
One‐year single group prospective analysis		
See Table 1	% with pharmacological intervention	Hypertension, diabetes mellitus, moderate‐to‐severe chronic kidney disease, atrial fibrillation, alterations in modifiable vascular risk factors compared to baseline, changes in SCORE2/SCORE2‐OP at the one‐year follow‐up, % adverse effects
Matched cohort long‐term analysis		
Demographics, vascular disease, comorbidities that can cause seizures, medical treatments	Stroke	Major adverse cardiovascular events, all‐cause mortality, stroke severity (NIHSS at stroke admission; modified Rankin Scale 3 months post‐stroke), conduction block/arrhythmia, and occurrence of recurrent seizures

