### Data analysis plan

2.5

Descriptive statistics will be presented as median (interquartile range) or number (%). For the single group study, we will use the normal approximation method to calculate 95% confidence intervals for proportions, including the primary outcome. Comparisons between baseline and one‐year follow‐up measurements will involve paired analyses, for example, McNemar's test for categorical data and paired t‐test or a non‐parametric equivalent for continuous data, depending on the data distribution. The analyses will be stratified by age groups, sex, and previously established cardiovascular risk factors. All tests will be two‐sided and considered statistically significant at *p* < 0.05.

The cohort study examines time to the different events of interest. We will use the Kaplan–Meier method and Cox proportional hazards regression to evaluate all‐cause mortality. For other events of interest, death will be accounted for as a competing risk. Survival times are calculated from the initial consultation until either the event of interest, death or study end, whichever comes first. To compare baseline group differences, we will utilize the Fisher exact test, the *χ*
^2^ test, or the Mann–Whitney *U* test, depending on the data characteristics. We do not anticipate any significant group differences; however, we will perform univariable and multivariable regression analyses to identify and adjust for any relevant covariates (age, sex, medical history, prescriptions of drugs used for cardiovascular prevention). Subgroup analyses will comprise previously “healthy” individuals (no drug prescriptions related to cardiovascular prevention) and individuals without established cardiovascular disease (defined as not being prescribed antiplatelet agents or anticoagulants). Analyses will also be stratified by age groups and sex.

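### The cohort subgroup without established cardiovascular disease is defined by drug prescriptions alone, with no date limit, although vascular diagnoses are already a cohort variable

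*Protocol article*

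**What the plan says.** Section 2.5 (Data analysis plan) of the protocol article names two cohort subgroups, and both are defined by prescriptions. The previously healthy are those with "no drug prescriptions related to cardiovascular prevention". Those without established cardiovascular disease are "defined as not being prescribed antiplatelet agents or anticoagulants". No diagnosis enters either rule, and neither definition gives a cut-off date or look-back.

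Other parts of the article bear on this:

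- Table 2 (section 2.4) lists the variables for the cohort analysis as "Demographics, vascular disease, comorbidities that can cause seizures, medical treatments", so disease and treatment are separate items.
- Section 2.4 counts starting or adjusting "lipid‐lowering agents, antiplatelet agents, or anticoagulants", among other classes, as the primary outcome of the single-group trial. A secondary outcome is the "proportion of cases where the screening procedure uncovers previously undetected vascular risk factors", with atrial fibrillation as one of the conditions.
- Section 2.3 takes cohort data from the National Patient Register, "which covers information on all specialized health care encounters in Sweden", and from the register of dispensed drugs. Prior stroke or TIA is an exclusion by diagnosis code.
- Section 2.5 starts follow-up at the initial consultation.

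**The concern.** A subgroup should contain the patients its label describes, and membership should be settled before the intervention can influence it. The rule falls short on the first count and leaves the second open.

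On the first, an antithrombotic prescription is only a proxy for cardiovascular disease, and the rule uses it although the diagnosis itself is among the planned variables. The subgroup will include some patients whose disease is on record. A result reported for people without established disease would then partly describe people who have it.

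On the second, antiplatelet agents and anticoagulants are among the drugs that screening may start. A rule with no date limit can be programmed so that a prescription issued because of screening changes a patient's subgroup. Patients seen before the practice change had no such screening, so the two eras could be selected differently.

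**Working it through.** The plan gives no size, event count or effect for this subgroup, so there is no figure to reproduce. The first two steps compare the text with itself. The third is an illustration on assumed inputs.

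**Step 1: classification.** Take a patient's status just before the initial consultation and apply the rule:

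| Vascular diagnosis on record | Antithrombotic | Class under the rule | Agrees with the label |
|---|---|---|---|
| no | no | without disease | yes |
| yes | yes | with disease | yes |
| yes | no | without disease | **no** |
| no | yes, for another reason | with disease | **no** |

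The third row needs only a diagnosis that does not always bring an antithrombotic. Prior stroke and TIA are excluded by code, but heart failure, atherosclerotic disease outside the brain and atrial fibrillation are not. A diagnosis code would identify these patients, and the plan already uses register codes for exclusions (section 2.3) and for myocardial infarction as an outcome (section 2.4). The mismatch does not depend on the time window.

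**Step 2: timing.** Section 2.3 sets dates for some criteria: before the initial consultation for stroke or TIA, and more than 3 months before it for earlier seizure codes and antiseizure drugs. It sets none for progressive brain disease. The subgroup rule sets none either. The words established and previously point to baseline status, but previously belongs to the other subgroup and neither word is a cut-off. Follow-up starts at the consultation, so a drug started because of screening will generally be dispensed after time zero.

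**Step 3: what the open timing could do.** Suppose that later prescriptions count and that screening has no effect on stroke. Let f be the share of the post-change subgroup that leaves because an antithrombotic is started, g the corresponding share of controls, and m the stroke risk of those who start relative to those who do not. The documents give none of these.

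With mean risk R before anyone leaves, and risk r in those who remain after a share f has left, R = r(f·m + 1 − f). The apparent post/pre risk ratio is therefore

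(g·m + 1 − g) / (f·m + 1 − f).

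- Removal from the post-change era only (g = 0), m = 2: f = 5% gives 1/1.05 = 0.95; f = 10% gives 1/1.10 = 0.91.
- The same, over f from 2% to 20% and m from 1.5 to 3: from 1/1.01 = 0.99 to 1/1.40 = 0.71.
- Equal removal, f = g: 1.00 for any m.
- More removal from controls, f = 5%, g = 10%, m = 2: 1.10/1.05 = 1.05.
- Only prescriptions before the consultation count, so f = g = 0: 1.00.

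The sign depends on the difference between f and g and on whether m exceeds 1.

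**The case against.** The strongest reply is that the rule is plainly meant as baseline status. It speaks of established disease, it shares a sentence with a subgroup described as previously healthy, and it follows text on baseline differences and covariates. The exact look-back is also detail that a condensed article may leave to the full protocol. Most of this stands: the missing date alone would be a request for clarification, and on the baseline reading the timing mechanism vanishes. It does not answer the classification problem, which concerns a definition the article does state.

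A second reply is that the drug proxy has a reason. The patient register covers specialized care only, while the drug register covers all dispensed prescriptions, so drugs can reveal disease managed elsewhere. This stands, and it is why the drug criterion should be kept and supplemented. Medical history is also a planned covariate, so diagnoses are not ignored throughout the analysis.

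A reader might go further and infer that the rule removes the highest-risk screened patients and so manufactures a benefit, with a ratio near 0.95 or 0.91. The documents do not support that. They do not say that later prescriptions count. Controls who start an antithrombotic would leave as well and, with a common study end, would have had longer to do so. The shares and the relative risk are assumptions.

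Nor do the documents say that screening is expected to matter most in this subgroup. Section 2.3 says only that benefit may be limited in patients already on prevention, which points rather to the healthy subgroup. A conflict of meaning with the single-group trial is likewise unproven: Table 1 lists history items without defining the label, and no comparison between the two components is planned.

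**Conclusion.** The concern holds as a defect of definition. Under any time window, patients with a recorded vascular diagnosis and no antithrombotic are placed in the disease-free subgroup, although the data to classify them correctly are already planned. How many are affected cannot be derived from the documents. On the baseline reading the same rule applies to both eras, so the error blurs the subgroup without evidently favouring either group.

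A bias between eras is conditional. It needs prescriptions at or after the consultation to count and the share starting these drugs to differ between eras, and its amount and direction cannot be fixed from the documents. The ratios above show only how sensitive the subgroup would be.

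The consequence is confined to subgroup results. The primary outcome, the main cohort comparison and the sample size are untouched. The change is still worth making before data extraction, because a better definition is available at almost no cost.

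**What to change.** In section 2.5, define established cardiovascular disease as either (a) a vascular diagnosis in the National Patient Register from a code list fixed in advance, or (b) a dispensed antiplatelet agent or anticoagulant. Both must be dated before the initial consultation, with one look-back length used in both eras. The subgroup is everyone with neither. State the same pre-consultation limit for the subgroup labelled healthy.

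Keeping criterion (b) means that a patient given an antithrombotic for another reason still falls outside the subgroup. That is acceptable as the price of catching disease managed outside specialized care.

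The cost is a sentence or two of text and a code list. The registers and the vascular disease variable are already in the plan. Compared with a drug-only rule applied at baseline, the subgroup becomes slightly smaller.

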### Sample size calculation

2.6

The incidence of late‐onset seizures is about 60 per 100 000 person‐years.^15^ Among these cases, approximately two‐thirds do not have an identifiable cause, such as a brain tumor. Participating health service regions cover about 5 million inhabitants and should have at least 1000 potential cases yearly. For the primary outcome of the single group analysis (proportion of cases undergoing pharmacological intervention), we aim for a margin of error less than 5%, which would translate to a minimum sample size of 385 (using an estimated proportion of 50%; for lower proportions, the required sample size generally decreases). For the cohort study, a 10‐year stroke risk of 10% and an effect of the intervention of 30% risk reduction translate to a need for 1021 participants post‐intervention and 2045 participants pre‐intervention to detect a difference in 10 years. Participating sites should cover approximately 1000 cases in the right age group per year, allowing inclusion of up to 2000 patients over 2 years and 4000 historic controls over 4 years. The vascular risk is not evenly distributed over time, the risk is greatest in the first years, but we should be able to detect a difference after 5–10 years.

### Patient and public involvement

2.7

The initiation phase will include contact with patient organizations in epilepsy and stroke in each participating health care region, to inform them about the study. Patient organizations will also be contacted for dissemination of the results after the study.

## ETHICS AND DISSEMINATION

3

The primary ethical consideration is that the screening process and the potential risk factors that may be identified could raise concern among the patients, but vascular risk factor screening is generally not perceived as stressful.^12^ This concern must be weighed against the possibility of preventing morbidity and mortality in patients with late‐onset seizures. Regarding safety considerations, opportunistic vascular risk factor assessment at health contacts is already advised in Sweden, the components of the intervention are already in clinical use, and all relevant drugs that may be prescribed are approved. Generally, side effects are mild and well‐documented. Importantly, the study protocol does not advocate any particular risk factor management strategies beyond what existing guidelines already recommend. The final study protocol, including the final versions of the informed consent form and other materials provided to participants, must be approved by the Swedish Ethical Review Authority. Any subsequent substantial changes to the protocol must be approved by all responsible investigators and the Swedish Ethical Review Authority before they can be implemented. Since ethical approval in Sweden requires resources and is only valid for 2 years, we will submit the ethical application only once funding has been obtained. We confirm that we have read the Journal's position on issues involved in ethical publication and affirm that this report is consistent with those guidelines.

### Consent

3.1

Informed consent will be mandatory for participation in the single group trial. The principal investigator at each site will ensure that subjects receive complete oral and written information about the study, its purpose, risks and benefits, and inclusion and exclusion criteria. The subject and the investigator shall then both sign the informed consent form (electronic signing will be available). Participants are free to discontinue participation at any time without providing a reason. The analysis of the long‐term stroke risks in the cohort study is an observational study using pseudonymized register data. For studies utilizing pseudonymized register data, the Swedish Ethical Review Authority typically grants a waiver of the informed consent requirement.

### Data access and confidentiality

3.2

Data collection for the single group study involves Electronic Case Report Forms (e‐CRFs) and recording relevant information in medical records. An electronic data capture system, REDCap, will be used for data management. The study database will be held at Sahlgrenska University Hospital, Gothenburg, Sweden. All data are stored in a pseudonymized manner. The subject information and the informed consent form will explain how study data are stored to maintain confidentiality in accordance with the General Data Protection Regulation (GDPR) and other relevant national data legislation. The National Board of Health and Welfare will provide pseudonymized register data for the cohort study.

### Dissemination plan

3.3

The results will be disseminated through peer‐reviewed scientific publications and presentations at relevant conferences.

## Data Availability

Being a study protocol, there is no data.
